### Methods for additional analyses (e.g. subgroup analyses) {20b}

Subgroup analysis defined by immunosuppressive treatment (everolimus) will be performed.

### Methods in analysis to handle protocol non-adherence and any statistical methods to handle missing data {20c}

Methods to handle missing data:

During the data collection stage by monitoring data quality. During the analysis stage before estimation of statistics.

For Missing Completely at Random (MCAR) and Missing at Random (MAR) data losses, the multiple imputation technique will be used, whereas for Missing Not At Random (MNAR) we will opt for pairwise.

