### Sample size {14}

For the primary endpoint (incisional hernia at 24 months), assuming a proportion in the control group of 20%^1^ and a proportion of 5% in the intervention group (prophylactic mesh reinforcement placement), with an alpha level of 0.05 and power of 80%, the sample size per group was calculated at 76 patients.

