## Statistical methods

### Statistical methods for primary and secondary outcomes {20a}

The primary analysis will be by intention-to-treat (ITT), including all randomized patients who have undergone renal transplantation. A per-protocol analysis will also be performed with all patients. Demographic and clinical parameters will be described by mean and standard deviation or median and its confidence interval for continuous variables depending on the normal or non-normal distribution of the sample. Categorical variables will be described by absolute and relative frequencies. In addition, differences between groups will be calculated using Student’s *t*-test or Mann–Whitney *U* test depending on the sample distribution and the chi-square test. Time to incisional hernia onset will be described by Kaplan–Meier survival analysis and compared by log-rank test. The analysis will include stratification by the variable “obesity”. A *p*-value < 0.05 will be considered statistically significant. We performed our analyses with Stata v16.1 (StataCorp, TX, USA).

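### The plan chooses its missing-data method by mechanism and handles data missing not at random by pairwise (available-case) analysis, which is generally biased there and cannot be triggered objectively

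*Protocol article*

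**What the plan says.** Section 20c of the protocol article ties the method to the mechanism. For MCAR and MAR losses, it says, "the multiple imputation technique will be used, whereas for Missing Not At Random (MNAR) we will opt for pairwise". No noun follows the last word; in a missing-data rule it ordinarily means pairwise deletion, that is, available-case analysis. The section does not say how the mechanism is to be decided, and nothing elsewhere in the article qualifies the rule.

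Section 20a sets the population: "The primary analysis will be by intention-to-treat (ITT), including all randomized patients who have undergone renal transplantation". Section 12 makes the primary outcome the proportion with incisional hernia at 2 years, compared by chi-square test, with Kaplan–Meier curves and a log-rank test for time to hernia. Section 14 plans on 20% in controls and "a proportion of 5% in the intervention group". Sections 11c and 18b expect good adherence to follow-up but give no dropout figure.

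**The concern.** There are two faults in the stated rule.

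- **The MNAR method does not address MNAR.** Under MNAR, whether a patient is missing depends on the unseen hernia status. Analysing only those who were seen then generally gives biased proportions. Available-case analysis is valid in general under MCAR, yet the rule reserves it for MNAR.
- **The rule cannot be applied objectively.** Observed data do not separate MAR from MNAR. Someone must decide which label applies, and so whether the primary comparison rests on imputation or on deletion, after seeing the data.

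The primary comparison is at stake. At 5%, about 4 hernias are expected among 76 mesh patients (0.05 × 76 = 3.8), so a few missing outcomes matter.

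**Working it through.** **Inputs from the protocol article.** Control 20%, mesh 5%, alpha 0.05, power 80%, 76 per group (section 14). **Assumed:** all missingness rates.

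**1. The plan's own figure.** Two-sided test, pooled variance, no continuity correction, mean proportion 0.125:

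n = [1.960·√(2·0.125·0.875) + 0.842·√(0.20·0.80 + 0.05·0.95)]² / 0.15² = (0.9167 + 0.3834)² / 0.0225 = 75.1, rounded up to **76**. This matches "the sample size per group was calculated at 76 patients". Power at 76 per group is 80.5%.

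**2. Formula.** Let p be the true rate, m1 the fraction missing among patients with a hernia and m0 among those without. The available-case rate is

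p(1−m1) / [p(1−m1) + (1−p)(1−m0)].

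**3. MNAR in controls only** (m1 = 30%, m0 = 5%; mesh 10% at random).
- Control: 0.20·0.70 / (0.20·0.70 + 0.80·0.95) = 0.14/0.90 = 15.6%.
- Mesh: 5.0%.
- Difference: **10.6 points** against a true 15.0. Power is 53%, against 76% with 10% lost completely at random in both arms.

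**4. The same losses with imputation under MAR.** Assume 25% of patients are obese, with control hernia rates of 35% (obese) and 15% (not obese), which average 20%. Imputation within arm and BMI stratum targets the observed stratum rates:
- Obese: 0.35·0.70 / (0.35·0.70 + 0.65·0.95) = 28.4%.
- Not obese: 0.15·0.70 / (0.15·0.70 + 0.85·0.95) = 11.5%.
- Weighted: 0.25·28.4 + 0.75·11.5 = 15.7%.
- Difference: 10.7 points by formula; a large simulation gave **10.8** (and 10.6 for deletion).

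Imputation under MAR is therefore almost as biased here. Its gain appears when losses are MAR: with 30% of obese and 5% of non-obese controls missing, the simulation gave 15.0 with imputation and 14.0 with deletion.

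**5. The same MNAR losses in both arms** (30%/5%).
- Control 15.6%; mesh 0.05·0.70 / (0.05·0.70 + 0.95·0.95) = 0.035/0.9375 = 3.7%.
- Difference: **11.8 points**.
- Odds ratio: true (0.20/0.80)/(0.05/0.95) = 4.75; observed (0.14/0.76)/(0.035/0.9025) = 4.75. It is preserved.

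**6. No true effect** (20% in both arms; controls 10% at random; MNAR in the mesh arm only).
- 30%/5%: mesh 15.6%, a spurious 4.4-point benefit; two-sided type I error about 10%.
- 40%/5%: mesh 0.12/0.88 = 13.6%, a spurious 6.4 points; about 17%.

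**7. Can the data show which branch applies?** In step 3 the control arm loses 0.20·0.30 + 0.80·0.05 = 10% and shows 15.6%. A control arm with a true rate of 15.6% and 10% lost completely at random shows exactly the same. The first case calls for pairwise under the rule and the second for imputation. The argument repeats within each BMI stratum.

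**The case against.** The strongest reply is that much of this can be read too strongly. Four such readings should be set aside.

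- **That the rule is backwards and the methods should be swapped.** Multiple imputation is right for MAR and acceptable for MCAR. Step 4 shows that standard imputation would not rescue the MNAR case either.
- **That the rule contradicts intention-to-treat.** Section 20a defines who belongs in the analysis; section 20c covers values missing within that set. Available-case handling weakens the analysis but does not directly contradict section 20a.
- **That the trial's conclusion is likely to flip.** Take 8 of 76 missing per arm, with 14/68 against 3/68 observed (p = 0.004, uncorrected chi-square). Let 2 of 8 missing controls have a hernia. With 4 of 8 missing mesh patients affected, 16/76 against 7/76 still gives p = 0.042. Significance is lost only at 5 of 8 (16/76 against 8/76, p = 0.075), when 62.5% of missing mesh patients have a hernia against 4.4% of those observed. Participant blinding and the matching drain (sections 11a and 17a) also make hernia-related loss in one arm only less plausible, though complications could differ by arm.
- **That imputation covariates or the handling of death are missing.** Those belong to a statistical analysis plan, which section 31c says will be shared.

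Two further points have some weight. Kaplan–Meier and log-rank analyses use follow-up before loss, and hospital records (section 9) may supply hernia status when a visit is missed. Both reduce the problem, but censoring related to hernia would bias the time-to-event analysis too. What remains is a rule stated outright, not a detail left for later: an analysis plan that followed it would inherit the fault.

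**Conclusion.** The concern holds for the MNAR clause and for choosing the method by mechanism. The clause is wrong as written: available-case analysis is generally biased under MNAR, and the condition that triggers it cannot be verified from the data.

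The effect cannot be fixed from the document, since every missingness rate above is assumed. In these examples the difference falls from 15.0 to 10.6 points (losses related to hernia in controls only) or to 11.8 points (the same in both arms, with the odds ratio unchanged). With no true effect and such losses in the mesh arm only, type I error rises to about 10% to 17%. The bias can therefore run either way, and it is small if few outcomes are missing. This should be fixed, but it does not by itself undermine the design.

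**What to change.** In section 20c, delete the pairwise clause and the selection of a method by diagnosed mechanism. State instead that:

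- missing 24-month hernia status is handled in the primary analysis by multiple imputation under MAR, whatever mechanism is suspected;
- departures from MAR are examined by a delta-adjusted or tipping-point sensitivity analysis that varies the two arms separately.

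The second item is essential, because imputation under MAR alone leaves most of the MNAR bias in place. Details of the imputation model can stay in the statistical analysis plan. The cost is a few lines of wording and one extra sensitivity analysis, with no new data and no change to the 76 per group.

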### Plans to give access to the full protocol, participant-level data and statistical code {31c}

Once the objectives of the project have been achieved, the data used will be deposited in the internal REDCap repository of IRYCIS, which is the Institutional Repository of the Ramón y Cajal Health Research Institute. Access to the internal repository data for other researchers who may be legitimately interested in them will be subject to the approval of an ethics commission.

Study Protocol, Statistical Analysis Plan (SAP), Informed Consent Form (ICF) and Clinical Study Report (CSR) will be publicly shared. Participant-level dataset will only be only accessible after the approval of an ethics commission.

## Oversight and monitoring

### Composition of the coordinating centre and trial steering committee {5d}

Not applicable. There is no steering committee. The Clinical Biostatistics Unit will constitute the data management team and data monitoring committee that it is independent from the sponsor and free of competing interests.

### Composition of the data monitoring committee, its role and reporting structure {21a}

Not applicable. There is no steering committee. The Clinical Biostatistics Unit will constitute the data management team and data monitoring committee that it is independent from the sponsor and free of competing interests.

### Adverse event reporting and harms {22}

Adverse events will be immediately communicated to the trial sponsor (Principal Investigator) by the patient, investigators of the trial or other care providers. A trial’s phone and e-mail contact will be provided to all trial participants.

### Frequency and plans for auditing trial conduct {23}

Not applicable.

### Plans for communicating important protocol amendments to relevant parties (e.g. trial participants, ethical committees) {25}

Principal Investigator (sponsor) will be responsible for communicating important protocol modifications including interruption or changes in recruitment of the study due to interim analysis results, to relevant parties: trial investigators, REC/IRBs and trial participants.

### Dissemination plans {31a}

The research team is committed to publish the results regardless of the direction of the study and statistical significance. For the publication of the results derived from the present study, the approval of all the investigators will be required. Likewise, the confidentiality of the identity of the participating subjects will always be respected. The trial has been registered at the ClinicalTrials.gov registry with the number NCT04794582 and the research team is committed to report the corresponding results at the end of the study.

## Discussion

Incisional hernia is a common complication after kidney transplantation with an incidence of 1.6–18.0% [1–4]. Several studies have identified multiple risk factors for the development of post-transplant incisional hernia that can be grouped into patient and donor factors, factors related to immunosuppression and factors related to the location and type of surgical incision [1–7]. Incisional hernia in transplantation is a poorly recognized pathology that is a source of morbidity and aesthetic concern for the transplanted patient. International guidelines on abdominal wall pathology recommend, in view of the limited scientific evidence, the performance of well-designed clinical studies to answer the usefulness and safety of the use of mesh reinforcement in abdominal closure in situations considered high-risk and lateral incisions, both characteristics of the surgical approach to transplantation [1, 17, 18].

Regarding patient-related factors, age > 50 years, female sex, obesity and cadaveric donor transplantation have been identified as potential risk factors. In view of the above, the renal transplant patient should have a higher risk of incisional hernia due to prolonged time on dialysis, immunosuppression and a high prevalence of comorbidities such as obesity, DM, chronic obstructive pulmonary disease (COPD) and hypertension [1, 2, 4]. In contrast, the incidence of incisional hernia in this population reported in the literature is lower than that reported for median laparotomy so the development of incisional hernia would appear to be related to factors specific to the surgical incision including, location, closure technique, tissue characteristics at the incision site and local biomechanical forces [4, 19].

Regarding factors specifically related to the surgical wound, the type of incision and surgical wound infection have been identified as risk factors [13, 19]. Different approaches to renal transplantation have been described including paramedial, oblique, extended groin, pararectal and field hockey stick incisions [1, 2, 4, 19]. Systematic reviews in the context of general surgery have shown that paramedian and transverse incisions have a lower incidence of incisional hernia [10, 11, 15, 20, 21]. The 2 most commonly used approaches are the oblique hockey stick approach from 2 cm above the anterior superior iliac spine to the pubis, involving the greater and lesser oblique and transverse muscles, and the external pararectal incision from 3 cm above the umbilicus to the pubis, involving the aponeurosis instead of the muscle. Paramedian incisions are similar to field hockey sticks and pararectal incisions in that they all use the lunate ligament at the lateral border of the rectus abdominis muscle to gain access to the retroperitoneal space in the iliac fossa. In contrast, oblique and extended inguinal incisions are also similar and extend laterally parallel to the muscle fibres of the external oblique. Studies comparing the incidence of incisional hernia between the field hockey stick incision and oblique incisions show, in principle, a lower incidence in the latter [2, 4, 19]. In fact, European surgical guidelines recommend transverse incisions not only because of a reduced incidence of incisional hernia but also because of a lower analgesic requirement [10, 15, 20]. Nanni et al. compared both types of incisions showing a reduction in the incidence of incisional hernia by abandoning the hockey stick incision and the extensive muscle section [19].

Regarding the surgical wound closure technique, there are no specific studies in the context of renal transplantation and we can only extend the recommendations established by the international guidelines for mid-laparotomy closure, which recommend the use of monofilament partially absorbable suture, with a gauge of 2/0 and mounted on a small size needle (26 mm) to perform a continuous monofilament suture taking an amount of tissue between 5 and 8 mm on each side and with stitches 5 mm apart (“small bites”) and keeping a ratio between the length of the suture and the length of the wound of at least 4/1 (4 cm of thread for each cm of wound) [20, 21]. There is no reference in the studies included in the systematic review to the use of the “small bites” technique or the use of prophylactic meshes that have been recommended in high-risk closures without a clear definition of the risk factors considered. On the other hand, in the context of transplantation, the potential risk of infection in the immunosuppressed patient should be taken into account when considering the use of mesh in surgical wound closure [2, 4, 9, 13].

Surgical infection is considered the main risk factor for incisional hernia formation. Bacterial proliferation induces an immune response that disrupts normal collagen synthesis and surgical wound healing. Organ dysfunction in the context of transplantation and immunosuppression are risk factors for surgical infection and thus for incisional hernia. Therefore, prophylaxis and aggressive treatment of surgical wound infection is a priority and will secondarily impact the risk of incisional hernia [2, 4, 13].

The relationship between obesity and incisional hernia may be determined by increased intra-abdominal pressure which increases mechanical stress on the incision, but obese patients also have an increased risk of surgical wound infection which may explain the increased incidence of incisional hernia [1, 2, 4, 7, 8].

Immunosuppressive regimen may be an important modifiable risk factor for the development of incisional hernia. Although several agents have been associated with an increased incidence of incisional hernia, specifically mycophenolate for its antiproliferative effect and sirolimus (m-TOR inhibitor), further studies are needed to definitively establish which immunosuppressive regimen is considered most appropriate [1, 2, 4, 8].

Muysoms et al. in 2017 conducted the review of all published articles on the use of prophylactic mesh reinforcement (excluding studies on para-stomal hernia prevention) with no restrictions on the type of study or qualitative analysis [20]. All data on the degree of contamination and number of wound and/or mesh infections were extracted and analysed. The use of prophylactic mesh reinforcement to prevent incisional hernias had been published in the literature in 1,759 patients, with an overall wound infection rate of 12% and a mesh infection rate of 0.6%. The procedure, it was concluded, could be considered safe and effective in both clean and clean-contaminated surgery. Regarding the position of the prophylactic mesh, both supraaponeurotic and retromuscular positions have been used. Both seem equally safe and effective and probably the position of the mesh will depend on the preference of each surgeon. However, to identify in which group of at-risk patient’s prophylactic mesh should be recommended, the authors conclude that further studies are needed. In contrast, the existing literature on the prophylactic use of mesh for wall closure in the context of renal transplantation is very scarce [22–25]. Of the 3 articles identified, 2 of them refer to their use for the prevention or treatment of compartment syndrome in renal transplantation [22, 23]. Beasley et al. use a propylene mesh as a bridge between the posterior fascial planes with the aim of achieving enlargement of the closure and reduction of the pressure exerted on the graft; in this way, the graft was saved in 15 of the 17 cases used, the associated complications being minor in all cases with the occurrence of 5 cases of seroma and 1 lymphocele. In 2015, Wood et al. publish the use of prophylactic polypropylene mesh in the prophylaxis of compartment syndrome in renal transplantation. Of a total of 134 patients in whom mesh was implanted only 1.5% developed surgical wound infection, a result similar to that of the non-implanted population (1.3%). The mesh removal rate was 6% (8/134). Only the article by Michalski et al. referred to the use of mesh for prophylaxis of early surgical wound complications [22]. A reduction, although not significant, of surgical wound complications was identified in the group in which closure reinforced with Vycril™ (polyglactin 910) resorbable mesh was used. No association was identified between the use of prophylactic mesh and the occurrence of surgical wound infections, a potential complication feared by the use of mesh in the context of immunosuppression and transplantation.

### Trial status

Protocol version 2.0. (02–18-2021).

Registered on 08 March 2021.

Recruitment is expected to start on 1 May 2021. Recruitment will be approximately completed in May 2023.

## Abbreviations

BMI: Body mass index
COPD: Chronic obstructive pulmonary disease
CSR: Clinical study report
DM: Diabetes mellitus
ICF: Informed consent form
IRB: Institutional review board
ITT: Intention-to-treat
MAR: Missing at random
MCAR: Missing completely at random
MNAR: Missing not at random
m-TOR: Mammalian target of rapamycin
PLA: Polylactic acid
SAP: Statistical analysis plan
REC: Research ethics committee
